New vector control tools should be user-friendly and not require much additional work from householders; they should be affordable, safe and effective in reducing vector densities below threshold levels estimated by the "pupae per person index"(4;5). There are many examples of potentially effective disease control products that have had only limited impact on the burden of disease because of inadequate implementation resulting in poor access. Implementation research has to help ensure that proven control products have the intended health impact. Implementation or distribution of tools of public health interventions consists of different components: geographical availability of product, economical affordability, acceptability of intervention and tool, demand for intervention, distribution strategies, …

Many diurnal human activities take place outside the house (schools, factories, …) and many individuals are potentially exposed to dengue transmission away from the household, therefore these places will be included in the intervention where possible. The difficulties and opportunities of inclusion of these sites in the tested strategies will be evaluated.

***Directly addressing these aspects, we will undertake a study, investigating the interaction between an ITM distribution (adult targeting) and community-based environmental management strategy (immature stages targeting) in a municipality of Cuba, where the baseline infestation already reached low levels, but where transmission still occurs. In this project, the tools will be delivered for free, so we will focus our research on the uptake, acceptability, effectiveness and cost-effectiveness of tools with or without a combined community-based environmental strategy.***

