## **B. Design of intervention:**

Curtains:

The insecticide-treated curtains (ITC) to be used are made from long-lasting, insecticide treated (pyrethroid deltamethrin is applied during manufacture) polyester netting that requires no re-impregnation (PermaNet®; Vestergaard-Frandsen company). PermaNet materials are special UV protected and retain their insecticidal properties and efficacy for about 2 years (information from producer). The material has been approved by WHOPES for use as bednets. Three insecticide impregnated curtains (ITC) will be distributed in each house: 2 window curtains, cut to fit the window opening (by preference not on the window towards the street, due to street-dust and hence frequent washing needed) and 1 door curtain (to be placed in a door-opening inside the house or on the closet or on the wall where no or minimal sunshine will touch the material - if a curtain is already hanging, the project-curtain can be attached to it).

All curtains will be white patterned netting and have a 1.6m width*2.2m height size (so that people can adapt them according their window and door size).

Before distribution the consent of the users will be procured in an informed consent-form designed for this project (see annex 2).

The curtains will be distributed with an accompanying promotion campaign: a Frequent Asked Questions document (FAQ) is already elaborated (see annex 3). It will be adapted and used during this campaign, together with other context-specific promotion materials.

The curtains will be distributed to the houses, but also to public places, as working areas, schools, cultural centra will be included as far as possible.

A replacement of curtains will be foreseen for the curtains in very bad condition. If new persons are coming to live in the circumscription during the study, they will be approached for their interest to be included in the study.

Assisted community-based environmental management

Main components of this strategy:

(a) establishment of a formal task force at circumscription level to drive the environmental management activities. This group identifies, designs and implements local environmental management actions, by actively involving the community

(b) intersectoral coordination between this task force and the existing governmental structures and sectors (education, promotion, water-supply, municipal services, …)

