(c) close collaboration between these task forces and the health system (especially the vector control programme).

Besides of the routine vector control programme, the assistance to set-up this intervention will be done by a local research group who will be responsible for its implementation, the coaching of the local task forces, coordination with the local health authorities, documentation of process and organization of training sessions according to the needs of the actors involved.

Distribution models for distribution of ITC

*Group I intervention*: the ITC will be distributed by the ‘operarios’ of the municipal routine vector control programme during their routine inspection visits. The communication campaign that will accompany the distribution will be designed by the municipal/provincial dengue control programme.

*Group II intervention*: The curtains will be distributed by the ‘trabajadores comunitarios’ and their local existing networks. The aim is that this model of distribution is a participatory one, where the way of distribution, promotion and communication is discussed within the existing community networks.

The Control-sites

In all areas, the routine control activities will be continued (only strategy in Group Control 1). The standard control activities are carried out by the programme’s vector control workers: entomological surveillance and source reduction through periodic inspection of houses, larviciding (with temephos) of water-holding containers, selective adulticiding (cipermethrine and clorpiriphus) when *Aedes aegypti* foci are detected, providing health education, promotion of community based environmental management and enforcing mosquito control legislation through the use of fines.

C. Study components, data collection and analysis:

1. Baseline investigation:
   1. Entomological survey:

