   4. Persistency testing of the curtains (monitoring insecticide content of PermaNet curtains over time): This will be tested by the standard WHO cone bioassays on a sub-sample of 10 curtains after 6 months of use and subsequently at approximately 6-month intervals. (Will probably be done in LSHTM, London or LSTM, Liverpool)

**Analysis**: Two major subjects:

1. The influence of (1) individual and household characteristics, (2) model of distribution and communication and (3) community involvement level will be evaluated on the effectiveness and ITC uptake measures.
2. The influence of adding an ITC strategy will be evaluated on the community involvement process and level reached.
3. Cost-effectiveness evaluation

We collected already the financial cost of the vertical programme during the two last years preceding the intervention and will calculate the average cost per house inspected and treated.

For each arm, we will multiply the number of houses inspected and treated annually during the study by the corresponding average cost described above, to calculate the total annual cost of the routine programme per arm.

We will calculate the total economic cost of the new control tool (curtain): The financial cost of the routine programme and economic cost of the community participating in the distribution, installation and maintenance of the tools; and the economic cost of the community participating in collective vector control activities.

The total annual cost of the different arms can be obtained adding the cost of the routine programme and the economic cost of the implemented strategy.

We also will calculate the average and marginal cost per house within arms and incremental cost per house between arms.

The activities of vertical programme will be costed prospectively during two years of the study, as well as the cost regarding the distribution of the tools itself. The cost information about the installation, maintenance, and participation in collective activities will be followed by community vector control workers during their routine activities and the corresponding questions will be included in the household surveys of uptake (taking place at least every 4 months) or acceptability, in 1 out of the 30 houses in all clusters.

We will obtain the effectiveness measure from the entomological study and use the difference between the baseline data and the data for the subsequent periods as effectiveness measure.

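### The itemised cost rule leaves out the purchase of the curtains and the cost of assisting the community strategy, and is unclear on how much routine-programme cost belongs in the curtain cost

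*Protocol*

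**What the plan says.** The costing rules stand in the Protocol under Cost-effectiveness evaluation, within part C (Study components, data collection and analysis).

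- Routine cost: houses inspected and treated in each arm are multiplied by an average unit cost, "to calculate the total annual cost of the routine programme per arm".
- Curtain cost: "We will calculate the total economic cost of the new control tool (curtain): The financial cost of the routine programme". The components after the colon read in full "The financial cost of the routine programme and economic cost of the community participating in the distribution, installation and maintenance of the tools", then, after a semicolon, "and the economic cost of the community participating in collective vector control activities".
- Arm total: obtained by "adding the cost of the routine programme and the economic cost of the implemented strategy".
- Data: the routine programme and the distribution of the curtains are costed prospectively. Installation, maintenance and collective participation are asked about in 1 of 30 houses in all clusters.
- Incremental ratio: difference in total cost divided by difference in effectiveness.
- Sensitivity analysis: varies the price of community time and the correlation between coverage and entomological outcome.

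The resources used are described elsewhere. Under Design of intervention, "Three insecticide impregnated curtains (ITC) will be distributed in each house"; worn curtains are to be replaced, and public places are supplied as far as possible. The Introduction says "In this project, the tools will be delivered for free". For the assisted community strategy, "the assistance to set-up this intervention will be done by a local research group who will be responsible for its implementation", with coaching, coordination, documentation and training among its duties.

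**The concern.** The resources that define the two strategies do not appear among the costs to be added up. A curtain strategy requires curtains to be bought, and an assisted community strategy requires someone to be paid to assist. Free delivery removes the price for households, not for the payer, and it means that household questions cannot recover the price.

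These costs arise only in some arms, so they do not cancel in an incremental comparison. The planned sensitivity analysis varies neither, so it would not reveal the gap. Because much of the costing is prospective, an item missing from the list may also go unrecorded.

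Separately, the curtain cost names the routine programme, and the arm total adds the routine programme again. Whether this repeats the same amount depends on how one sentence is read. What is at stake is the answer to specific objective 3; the primary entomological comparison is not affected.

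**Working it through.** The protocol states no price, cost or ratio, so there is no figure of its own to reproduce. The check is a count of curtains followed by cost algebra.

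**Curtains without a listed purchase cost (Annex 1, three per house)**

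- Intervention 1: 367 + 356 + 422 = 1,145 houses; 3 × 1,145 = 3,435 curtains.
- Intervention 2: 658 + 649 + 433 = 1,740 houses; 3 × 1,740 = 5,220 curtains.
- Together: 2,885 houses and 8,655 curtains, before replacements and public places.

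At an assumed price of 2 to 10 currency units per curtain, this is 6 to 30 per house (17,310 to 86,550 in all). Spread over the producer's figure of about 2 years of insecticidal life, it is 3 to 15 per house-year. The price range is an assumption.

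**Algebra, per house-year.** R = routine programme; P = curtain purchase; D = effort on distribution, installation and maintenance; A = research-group assistance. Collective activity time is left aside because it is listed and is to be asked about in all clusters.

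Full cost: Control 1 = R; Control 2 = R + A; Intervention 1 = R + P + D; Intervention 2 = R + P + D + A.

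There are two readings of the curtain cost as listed:

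- *Counted once*: the programme enters only for its distribution effort, so a curtain arm costs R + D.
- *Literal*: the whole programme enters, so a curtain arm costs R + (R + D).

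Error (listed minus full incremental cost):

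| Comparison | Counted once | Literal |
| --- | --- | --- |
| Intervention 1 vs Control 1 | D − (P + D) = −P | (R + D) − (P + D) = R − P |
| Intervention 2 vs Control 2 | −P | R − P |
| Control 2 vs Control 1 | −A | −A |
| Intervention 2 vs Intervention 1 | −A | −A, apart from any difference in R between these arms |

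**Illustration for Intervention 1 vs Control 1.** R is set to 1; P and D are assumed values.

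| P | D | Full (P + D) | Counted once (D) ÷ full | Literal (1 + D) ÷ full |
| --- | --- | --- | --- | --- |
| 0.1 | 0.1 | 0.2 | 0.50 | 5.5 |
| 0.1 | 0.5 | 0.6 | 0.83 | 2.5 |
| 1 | 0.1 | 1.1 | 0.09 | 1.0 |
| 1 | 0.5 | 1.5 | 0.33 | 1.0 |
| 2 | 0.1 | 2.1 | 0.05 | 0.52 |
| 2 | 0.5 | 2.5 | 0.20 | 0.60 |

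The difference in effectiveness is the same whichever cost is used, so each factor carries straight through to the incremental ratio. Counted once, the ratio is always too low. On the literal reading it is too high when P is below R, correct when they are equal, and too low when P exceeds R.

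**The case against.** The best defence is that the governing terms are broad. A total economic cost of the curtain, and the cost of whichever strategy an arm implements, could be meant to include purchase and assistance. Control 2 has a strategy but no curtain, so the strategy term must reach beyond the curtain list. A purchase price would not be expected in a paragraph on prospective and household data, and a separate economic plan may give the detail. This tempers the claim: the ratios would be biased if computed as listed, and it is not shown that they will be. It does not remove the point, because the protocol fixes a component list, an arm-total rule and sensitivity parameters, and the list does not match the interventions described.

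Three stronger readings are tempting and are not supported:

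- *The routine programme is counted twice.* This follows from the literal grammar, but the words on taking part in distribution can apply to the programme as well as to the community. That fits Intervention 1, where programme workers hand out the curtains on routine visits. The sentence is ambiguous; a double count is not established.
- *Curtains will certainly look too cheap.* This holds only if the programme is counted once. On the literal reading the sign of R − P cannot be told.
- *Collective community time is wrongly charged to curtains.* A semicolon sets that item apart, and it is to be asked about in all clusters.

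It is also fair to say that the assumed price range shows nothing about distortion of the ratio, since no routine cost or effect is available to set against it.

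**Conclusion.** The point holds in this form: the itemised cost definition omits curtain acquisition (about 8,655 curtains for 2,885 houses, plus replacements and public places) and the research group's assistance, and it is ambiguous on the routine programme. With that programme counted once, ratios computed as listed would understate the incremental cost of curtain over no-curtain arms by P, and of assisted over non-assisted arms by A. If the whole programme also sits inside the curtain cost, the curtain error is R − P and its direction is unknown.

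The curtain count assumes that every Annex 1 house accepts three. The per-house algebra assumes that P and A are not recorded under another heading. No absolute error in the ratios can be derived from the document. The matter affects a specific objective and a secondary outcome, so it should be corrected, but it does not touch the primary outcome.

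**What to change.** Rewrite the cost definitions as follows.

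- Curtain cost: purchase of all curtains, including replacements and those for public places, annualised over the stated life of about 2 years; plus the programme's and the community's distribution effort; plus community time for installation and maintenance.
- Community strategy cost: research-group assistance and training, plus task-force time.
- Community time for collective activities: recorded in every arm where it occurs.
- Arm total: routine programme counted once, plus the cost of each strategy allocated to that arm.
- Sensitivity analysis: add curtain price and useful life to the parameters varied.

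The change is mainly wording. It requires retrieval of purchase and staffing records, and the protocol does not say whether these are already held. The ratios will probably be less favourable to the strategies.

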# IV. Methodology

## IV.A. Description of study and Research design

A. Description of study and study areas
Area Sur and Centro of Guantanamo were identified as the areas where the study sites will be selected from. Both areas have high infestation-levels in comparison to other areas of Guantanamo municipality.

The circumscriptions (lowest geopolitical unit, containing approx. 500 houses) were identified as unit of intervention and of analysis of effectiveness.

Circumscriptions with the highest infestation –levels will be selected and afterwards the allocation to control or intervention group will be on a random basis. The circumscriptions with a common boundary will be eliminated from the study, as a certain spill-over effect is expected (3).

Design:

Cluster-randomized controlled trial, Latin square design

|  | ITC Distribution | No ITC distribution |
| --- | --- | --- |
| Assisted CB environmental management | Group Intervention 2 | Group Control 2 |
| No assisted CB environmental management | Group Intervention 1 | Group Control 1 |

*Group Intervention 1*: Distribution of Curtains, no assisted community-based (CB) environmental management

*Group Intervention 2*: Distribution of Curtains + assisted CB environmental management

*Group Control 1*: No curtains, no assisted CB environmental management

*Group Control 2*: No curtains, assisted CB environmental management

Sample size estimation (based on the effectiveness of curtains measured through entomological indices):

The cumulative house index over 1 year is estimated at 2%.

We estimate that we can decrease the infestation-levels with 75% in the ITC intervention strategy in comparison with no intervention. Based on the Hayes and Bennett sample size estimation (6), we need 6 clusters of 500 houses in each arm (‘ITC distribution’ and ‘no ITC distribution’) to demonstrate the effect of the curtain-intervention (power of 80%). The subdivision of each arm in 2 groups makes it possible to 1) measure the influence of adding an ITC strategy on top of the community involvement process and 2) the influence of community involvement on the ITC uptake.

(Annex 1)

Duration of study: Primary and secondary outcomes will be evaluated over a period of 2 years.

Outcomes:

*Primary outcome:*

Effectiveness: cumulative house index (on year basis) and other *Aedes* infestation indices

*Secondary outcomes:*

- Uptake and use of IT curtains

- Satisfaction with IT curtains

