Average cost-effectiveness will be calculated, dividing the cost by the effectiveness estimate for the corresponding period; also, incremental cost-effectiveness will be calculated by dividing the difference in total cost by the difference in effectiveness between the strategies.

The robustness of the cost effectiveness estimate we will evaluate performing the sensitivity analysis, varying the price of the community time, and using the variation observed in the correlation between the coverage of tools and the corresponding entomological outcome.

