***Annex 1: Cluster-allocation***

| **Intervention** | **Circumscriptions** | **Number of blocks/circumscription** | **Number of houses/circumscription** |
| --- | --- | --- | --- |
| **Intervention 1:**  **Routine programme + Curtains** | 45 | 7 | 367 |
| 144 | 10 | 356 |
| 30 | 9 | 422 |
| **Intervention 2:**  **Routine programme + Curtains + assisted Community participation** | 194 | 12 | 658 |
| 124 | 2 | 649 |
| 69 | 9 | 433 |
| **Control 1:**  **Routine programme** | 51 | 17 | 791 |
| 198 | 4 | 350 |
| 48 | 5 | 199 |
| **Control 2:**  **Routine programme+ assisted community participation** | 47 | 12 | 795 |
| 38 | 10 | 576 |
| 29 | 8 | 410 |

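### The incremental cost-effectiveness ratio sets a difference in total arm cost against infestation indices that do not grow with arm size, so unequal numbers of houses enter the ratio as if they were strategy cost

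*Protocol*

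**What the plan says.** The relevant text is the cost-effectiveness evaluation in the Protocol, part C (Study components, data collection and analysis).

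- Routine cost: "For each arm, we will multiply the number of houses inspected and treated annually during the study by the corresponding average cost described above".
- Arm total, with the arm's own strategy as the second component: "The total annual cost of the different arms can be obtained adding the cost of the routine programme and the economic cost of the implemented" (cut before its last word).
- Per-house costs, as a further output: "We also will calculate the average and marginal cost per house within arms and incremental cost per house between arms".
- Effect: the plan is to "use the difference between the baseline data and the data for the subsequent periods as effectiveness measure", with the data taken from the entomological study.
- Incremental ratio: "incremental cost-effectiveness will be calculated by dividing the difference in total cost by the difference in effectiveness between the strategies".

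The outcomes list in section IV.A gives "Effectiveness: cumulative house index (on year basis) and other *Aedes* infestation indices". The monitoring section names the house index, the Breteau index and the pupal index per inhabitant. The column "Number of houses/circumscription" in Annex 1 shows how many houses each circumscription holds. The planned sensitivity analysis varies the price of community time and uses the variation in the relation between coverage and entomological outcome. It does not deal with arm size.

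**The concern.** A cost-effectiveness ratio needs a numerator and a denominator on the same base. Here the numerator is a sum over all houses in an arm, while every effectiveness index named is a rate per house or per inhabitant. With equal arms this would only change the unit of the ratio. The arms are not equal: the largest has 1.56 times the houses of the smallest (1,781/1,145). The difference in total cost then mixes two things, the extra cost of the strategy and the cost of running the routine programme in more or fewer houses.

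At stake is specific objective 3 (section III.B), the cost-effectiveness of the curtains alone and in combination. Followed literally, the rule favours curtains alone over routine control, because the curtain group is smaller. It penalises adding community-based management, because both assisted groups are larger.

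**Working it through.** The protocol states no arm cost and no ratio, so there is no figure of its own to reproduce.

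**Houses per group (Annex 1)**

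- Intervention 1 (I1): 367 + 356 + 422 = 1,145
- Intervention 2 (I2): 658 + 649 + 433 = 1,740
- Control 1 (C1): 791 + 350 + 199 = 1,340
- Control 2 (C2): 795 + 576 + 410 = 1,781

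**Notation.** Per house and year, r is the routine cost, c the added curtain cost and m the added cost of community-based management. The protocol gives none of these, so c and m are expressed as multiples of r. I take r as equal in all arms and, for illustration, c and m as constant per house.

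**Difference in total cost under the written rule**

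- I1 v C1: 1,145(r + c) - 1,340r = 1,145c - 195r
- C2 v C1: 1,781(r + m) - 1,340r = 1,781m + 441r
- I2 v I1: 1,740(r + c + m) - 1,145(r + c) = 1,740m + 595(r + c)
- I2 v C2: 1,740(r + c + m) - 1,781(r + m) = 1,740c - 41(r + m)

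**No added cost (c = m = 0).** The differences should be 0. They are -195r, +441r, +595r and -41r. These terms are arm size alone and need only the Annex 1 counts.

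**With added cost.** The table divides the written numerator by the added cost actually incurred in the first-named arm (1,145c, 1,781m, 1,740m and 1,740c). A value of 1 means no distortion. Where both strategies enter, c = m.

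| Added cost per house | I1 v C1 | C2 v C1 | I2 v I1 | I2 v C2 |
| --- | --- | --- | --- | --- |
| 0.25r | 0.32 | 1.99 | 2.71 | 0.88 |
| 0.5r | 0.66 | 1.50 | 2.03 | 0.93 |
| r | 0.83 | 1.25 | 1.68 | 0.95 |
| 2r | 0.91 | 1.12 | 1.51 | 0.96 |

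For example, at c = r the first comparison gives (1,145 - 195)/1,145 = 0.83, and at m = r the second gives (1,781 + 441)/1,781 = 1.25.

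**Sign.** The I1 v C1 numerator is zero at c = 195r/1,145 = 0.17r. Below that, curtains would appear to save money although they add cost in every house.

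**Per-house numerator.** Under the same assumptions the four differences are c, m, m and c, whatever the arm sizes.

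**The case against.** The best counter-argument is that total cost need not mean the arm total. The section also uses total for the sum of cost components, and it plans an incremental cost per house between arms, so a per-house total is a possible reading. It is the less natural one: the total annual cost of the arms has just been defined as a sum over houses plus strategy cost, and the per-house figures are introduced as additional results that the ratio does not mention.

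Several other objections stand and limit the point.

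- Only the routine component is strictly proportional to houses. It counts houses inspected and treated, which may differ from the Annex 1 numbers. Community-based management rests on a task force per circumscription, so part of its cost may be fixed there. The routine size terms remain.
- A reader might infer that the average ratios also rank the arms by size. The text says only that the cost is divided by the effectiveness estimate. Size enters only if that cost is the arm total and the effect is an index. If the effect were a change in counts of foci, the number of houses would cancel in the average ratio, though not in general in the incremental one.
- A reader might infer that curtains will wrongly look cost-saving. That requires c below 0.17r, and the protocol gives no unit cost to show it.
- A reader might infer that every comparison is badly distorted. Intervention 2 v Control 2, which isolates curtains on top of community work, differs by only 41 houses.
- Cost-effectiveness is a secondary outcome. The primary outcome, sample size and data collection are untouched, and the correct ratio can be computed later from planned quantities.

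**Conclusion.** The point holds for the incremental ratio. On the natural reading, the written rule carries size terms of -195r, +441r and +595r in three comparisons and -41r in the fourth. If the added strategy cost per house equals r, the numerator is about 17% too low for Intervention 1 v Control 1 and 25% too high for Control 2 v Control 1. The distortion grows as strategy cost falls relative to routine cost and shrinks as it rises.

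The size terms rest on the Annex 1 counts, an equal routine cost per house in all arms, and an effect measured on one of the named indices. The percentages also rest on assumed unit costs. The documents do not support a firm claim that the sign reverses, nor that the average ratios are wrong. Because this is a stated rule that gives a distorted result, and not a detail left open, it should be corrected. It does not threaten the trial's main result.

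**What to change.** In the incremental ratio, replace the difference in total cost with the difference in annual cost per house, that is, the incremental cost per house that the section already plans. Scaling every arm to one common number of houses would serve equally well. In addition:

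- state that the average ratio uses the same cost basis;
- match the cost unit to the effect unit: per house for house-based indices, per inhabitant if pupae per inhabitant is the effect, and both cost and effect per 1,000 houses if foci averted is the effect;
- report total arm cost descriptively only.

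The change is essentially one sentence and needs no new data. It has two consequences. The ratio for curtains alone will look less favourable than under the written rule. Community-strategy costs that are fixed per circumscription will still vary per house with cluster size, so the per-house figure is not fully free of size, and the report should say so.
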